#### **\*\*3.6 Study Procedures\*\***

Study steps mainly include clinical trial randomization and grouping, follow-up and data collection at baseline (T0), at 2 weeks of treatment (T1), at the end of 4 weeks (T2), and at 8 weeks after treatment completion (T3), as detailed below:

- (1) **\*\*Randomization and Grouping:\*\*** Enroll eligible stroke patients with motor dysfunction and assign them to the Conventional Treatment Group, Left-sided taVNS Group, or Bilateral

taVNS Group using a random number table.

(2) **\*\*Collection of Basic Patient History Information:\*\*** Collect basic information for enrolled subjects, including age, gender, time since onset, stroke type, education level, marital status, etc.

(3) **\*\*Data Collection at T0, T1, T2 time points:\*\*** Fugl-Meyer Assessment for Upper Extremity (FMA-UE) and Lower Extremity (FMA-LE), Wolf Motor Function Test (WMFT), Balance evaluation and training system, Berg Balance Scale (BBS), Holden Functional Ambulation Classification (FAC), Modified Barthel Index (MBI), functional Near-Infrared Spectroscopy (fNIRS).

(4) **\*\*Data Collection at T3 follow-up time point:\*\*** Follow up via phone or outpatient visit to collect Berg Balance Scale (BBS) and Modified Barthel Index (MBI) scores at 8 weeks after treatment completion.

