handle repeated measures data, implemented via the "nlme" package in R, to assess changes over time and differences between groups, accounting for correlations within subjects across multiple time points. Post-hoc subgroup analyses will explore differential efficacy of taVNS across different stroke types (ischemic vs. hemorrhagic) and lesion locations. 
 For safety indicators, normality tests will first be performed on Heart Rate Variability (HRV) and blood pressure data. If normally distributed, paired sample t-tests will be used to compare values before and during treatment; if not, Wilcoxon signed-rank test will be used. Comparison of adverse event incidence rates between groups will use Chi-square test or Fisher's exact test.  $p < 0.05$  will be considered statistically significant. |

| **\*\*Study Duration\*\*** | This project is expected to be completed in 3 years (January 2025 --- December 2027). |

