#### **\*\*3.3 Study Groups and Interventions\*\***

To verify the clinical efficacy and safety of bilateral taVNS for stroke motor dysfunction, and its difference compared to unilateral left-sided taVNS, this clinical trial is divided into three groups:

- (1) **\*\*Conventional Treatment Group:\*\*** Based on drug therapy, provide conventional rehabilitation treatment for stroke hemiplegic motor dysfunction, including comprehensive rehabilitation such as exercise therapy, occupational therapy, physical agent therapy, conventional acupuncture, etc.
- (2) **\*\*Left-sided taVNS Group:\*\*** Based on the conventional treatment group, provide classic non-invasive left-sided auricular vagus nerve electrical stimulation. taVNS parameters: left ear, frequency 25Hz, pulse width 300us, current 6 mA.
- (3) **\*\*Bilateral taVNS Group:\*\*** Based on the conventional treatment group, provide non-invasive bilateral auricular vagus nerve electrical stimulation. taVNS parameters: both ears, frequency 25Hz, pulse width 300us, current 6 mA.

**\*\*taVNS Treatment Regimen:\*\*** 30min/session, 2 sessions/day, 6 days/week, for 4 weeks.

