**\*\*10. Expected Schedule and Completion Date\*\***

This project is expected to be completed in 3 years. The overall schedule and progress are as follows:

[January 2025 - June 2025]{.underline}

Prepare and refine all pre-trial tasks, explain patient inclusion and exclusion criteria, conduct standardized training for scale administration, and provide homogeneous training for taVNS treatment to achieve standardized homogeneity across the three clinical centers. Additionally, complete ethics applications and approvals at the three clinical centers, and complete registration on the Chinese Clinical Trial Registry website.

[July 2025 - June 2026]{.underline}

Begin enrolling stroke patients first in the Rehabilitation Medicine Department of the First Affiliated Hospital of Nanchang University, administer taVNS treatment, monitor safety, and perform assessments including FMA-UE, FMA-LE, WMFT, Balance evaluation and training system, BBS, FAC, MBI, and fNIRS.

[July 2026 - December 2027]

Simultaneously initiate trial enrollment in the Rehabilitation Medicine Departments of The Rehabilitation Hospital Affiliated to Nanchang University and The First Affiliated Hospital of Gannan Medical University, administer taVNS treatment, monitor safety, and perform assessments including FMA-UE, FMA-LE, WMFT, Balance evaluation and training system, BBS, FAC, MBI, and fNIRS.

[December 2027 - June 2028]

Conduct supplementary clinical trials, data collection and processing, statistical analysis of experimental data, manuscript writing, and final reporting.

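### The protocol lets the 8-week Berg Balance Scale be collected by telephone, which cannot give a score comparable with the in-person scores it is modelled with

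*Protocol*

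**What the plan says.** Section 3.6 sets four assessments: T0, T1 (2 weeks), T2 (end of the 4 weeks) and T3, "at 8 weeks after treatment completion (T3").

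- Item (3), headed "Data Collection at T0, T1, T2 time points", lists the full battery, including the Fugl-Meyer scales, BBS, MBI and fNIRS.
- Item (4) covers T3: "Follow up via phone or outpatient visit to collect Berg Balance Scale (BBS"), and the same sentence goes on to the MBI. Both modes of contact are given for both scales.
- Section 3.8.2 lists BBS and MBI as secondary endpoints.
- Section 6.2 names BBS among the outcomes for a linear mixed model over the repeated time points. It does not mention mode of collection.
- Section 3.3 gives the conventional group rehabilitation alone, with no sham stimulation, although section 3.5 declares the trial double-blind.

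On dates, the synopsis says "This project is expected to be completed in 3 years" and ends the study in December 2027. Section 10 repeats the 3 years. Its list of periods, however, has enrolment, treatment and assessment running in "July 2026 - December 2027", followed by a further period, including data collection, to June 2028.

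**The concern.** The BBS is an observed performance scale: an assessor watches balance tasks and scores them. What comes back over the telephone is the patient's or a relative's account of balance, which is a different measurement. T3 is the only BBS assessment after treatment has stopped, so it carries whatever the trial reports about balance at follow-up.

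Two features make the mixing more than noise. First, in a hemiplegic population the less mobile patients are plausibly the ones who are phoned, so mode would be related to the outcome itself. Second, patients in the conventional group know that they receive no stimulation, so self-reported balance is open to arm-related reporting in a way that an observed score is not. If the phone values enter the model as ordinary BBS scores, the T3 contrast between arms may reflect the way the data were collected as well as the treatment.

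**Working it through.** **Comparability of modes**

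1. T0 to T2 are in-person assessments. Item (3) does not say so outright, but it includes fNIRS and observed motor tests, and T1 and T2 fall during or at the end of a course given at "30min/session, 2 sessions/day, 6 days/week, for 4 weeks".
2. T3 may be by phone or visit, for BBS as well as MBI (item (4)).
3. BBS is analysed over its repeated time points in one mixed model (section 6.2). On a plain reading this includes T3.
4. Let p be the share of T3 BBS values taken by phone in an arm, and e the mean error of a phone value against an observed score. The T3 mean in that arm is shifted by p × e. The contrast between arms A and B is shifted by p_A × e_A − p_B × e_B. If p and e are equal in the two arms, the shift cancels in the contrast but remains in the change from T2 to T3. If the error differs between arms by D and the phone share p is equal, the contrast is biased by p × D. For an assumed p of 20% to 60%, that is 0.2D to 0.6D.

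**Number of values affected**

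- Section 6.1 plans 34 per group before the 10% dropout allowance, so about 3 × 34 = 102 patients reach T3 if dropout is as planned.
- Each 10% by phone is 0.10 × 102 ≈ 10 values. An assumed 20% to 60% gives 0.20 × 102 ≈ 20 to 0.60 × 102 ≈ 61.
- The documents give no phone share, so this range is illustrative only. The true number could be none or all.

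**Dates**

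- Stated duration: January 2025 to December 2027 = 36 months.
- Section 10 periods: January to June 2025 (6) + July 2025 to June 2026 (12) + July 2026 to December 2027 (18) + the remainder to June 2028 (6) = 42 months. The 3 years is not reproduced.
- T3 falls 4 + 8 = 12 weeks after treatment starts (taken here as the enrolment date). Enrolment on 1 December 2027 puts T3 on 23 February 2028; enrolment on 31 December 2027 puts it on 24 March 2028.
- For T3 to fall by 31 December 2027, treatment must start by 8 October 2027. For T3 by 30 June 2028, it must start by 7 April 2028.
- T3 of a December 2027 enrolee therefore fits the June 2028 end but not the December 2027 end. No last-enrolment date is given.

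**The case against.** The best defence is that item (4) is loosely worded shorthand: sites will see patients for the BBS and use the phone for the MBI, and handling of mode can be left to a statistical analysis plan. Part of this stands. BBS at a visit is sound, the MBI can plausibly be obtained by interview, and model details may properly sit in an analysis plan. But the mode of collection is fixed in the protocol, the sentence as written permits a phoned BBS, and no later analysis turns a telephone account into an observed score.

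It is also fair that the documents do not describe how the BBS is scored, do not say who would be phoned, and declare the trial double-blind. The first rests on the nature of the scale, which is hardly in dispute. The link with mobility is a plausible inference, not a documented fact. The link with arm follows from the absence of a sham in section 3.3 and is likewise a possibility, not a demonstrated effect.

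Visit-only BBS has its own weakness: if the less mobile do not attend, the missing values depend on mobility. This is a reason to state the missing-data assumption and test it, not to accept phone scores.

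Three stronger readings are tempting:

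- *The follow-up is useless.* The protocol states no purpose for T3, and both the visit BBS and the MBI remain usable.
- *The Fugl-Meyer scales must be added at T3.* They are consistently placed at T0 to T2 ("Fugl-Meyer Assessment for Upper Extremity (FMA-UE) and Lower Extremity (FMA-LE), Wolf Motor Function Test (WMFT" and the rest of item (3)). No section promises them at T3 or sets a durability objective. Their absence limits what can be said about persistence of the primary effect, but it is not an error.
- *Late enrolees will lose their T3.* Section 10 continues data collection to June 2028, which is late enough. A count of patients affected would need a last-enrolment date and an accrual pattern; the first is not given, and the staged opening of centres argues against even accrual.

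**Conclusion.** The point holds for the telephone BBS. As written, section 3.6 item (4) allows non-comparable values of a secondary endpoint into the model at its only post-treatment assessment. The size cannot be fixed from the documents: about 10 T3 values for each 10% collected by phone, assuming 102 patients reach T3, with bias between arms only if phone share or reporting error differs by arm. The analysis of the primary endpoint over T0 to T2 is unaffected. This should be corrected before T3 data are collected, because it cannot be repaired afterwards.

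The date discrepancy is real but minor: 36 months stated against 42 scheduled. It is a contradiction to reconcile, not evidence of lost follow-up.

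**What to change.** Amend section 3.6 item (4) as follows:

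- At T3, BBS is scored only at an outpatient visit. A telephone contact collects the MBI only.
- The mode of contact is recorded for every T3 assessment.
- Where contact was by phone, BBS is set to missing. The mixed model then uses the observed scores under missing at random given the earlier scores.
- Because absence from the visit may depend on mobility beyond what earlier scores capture, a sensitivity analysis departs from that assumption, for example by shifting the missing T3 BBS values downward by a range of amounts, in all arms and by arm.

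Separately, reconcile the 3 years to December 2027 in the synopsis and section 10 with the schedule to June 2028, and state a last-enrolment date consistent with whichever end date is kept.

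The cost is a short amendment, one extra recorded item, and more missing T3 BBS values with some loss of precision at that visit. No change to sample size or to the T0 to T2 assessments is needed.

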### **\*\*3.7 Concomitant Treatment\*\***

Based on drug therapy, provide conventional rehabilitation treatment for stroke hemiplegic motor dysfunction.

### **\*\*3.8 Endpoint Evaluation Measures\*\***

#### **\*\*3.8.1 Primary Endpoint Evaluation Measures\*\***

- > (1) Fugl-Meyer Assessment for Upper Extremity (FMA-UE)
- > (2) Fugl-Meyer Assessment for Lower Extremity (FMA-LE)

#### **\*\*3.8.2 Secondary Endpoint Evaluation Measures:\*\***

- > (1) Wolf Motor Function Test (WMFT)
- > (2) Balance evaluation and training system, Berg Balance Scale (BBS)
- > (3) Holden Functional Ambulation Classification (FAC)
- > (4) Modified Barthel Index (MBI)
- > (5) functional Near-Infrared Spectroscopy (fNIRS)
- > (6) functional Magnetic Resonance Imaging (fMRI)

### **\*\*4. Safety Evaluation\*\***

#### **\*\*4.1 Adverse Events\*\***

##### **\*\*4.1.1 Definition\*\***

> **\*\*Adverse Event (AE):\*\*** Any untoward medical occurrence or worsening of a pre-existing medical condition in a subject temporally associated with the use of the investigational intervention, regardless of whether it is considered causally related. An untoward medical occurrence can be a symptom (e.g., nausea, chest pain), sign (e.g., tachycardia, hepatomegaly), or abnormal finding (e.g., laboratory test, ECG). Worsening of the disease under investigation and its associated symptoms or signs, if judged by the investigator to be expected, is not considered an AE.

>

> **\*\*Serious Adverse Event (SAE):\*\*** An adverse event occurring during the study that meets one or more of the following criteria: results in death, is life-threatening, requires inpatient hospitalization or prolongation of existing hospitalization, results in persistent or significant disability/incapacity, or severely disrupts activities of daily living, results in a congenital anomaly/birth defect, etc.

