## **\*\*2. Study Objectives\*\***

2.1 **\*\*Primary Research Objective:\*\*** This project aims to observe the therapeutic effect of bilateral taVNS on motor dysfunction reconstruction after stroke, and to elucidate its brain function rehabilitation mechanism using fNIRS and fMRI technology, thereby laying a theoretical foundation for the clinical application of bilateral taVNS in treating post-stroke motor dysfunction.

2.2 **\*\*Secondary Research Objective:\*\*** To study the safety of unilateral taVNS in treating stroke patients.

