#### **\*\*4.2 Adverse Event Handling, Follow-up, and Serious Adverse Event Reporting\*\***

> The investigator shall explain in detail to the subject, requiring the subject to truthfully report any changes in condition after receiving the intervention treatment. Physicians should avoid leading questions. While observing efficacy, close attention should be paid to adverse events, analyzing causes and making judgments. For any AE occurring during the study, details such as time of onset, symptoms, duration, measures taken, and outcome should be recorded in the medical record/Case Report Form, and its relationship to the investigational intervention should be assessed; for those with abnormal laboratory findings, follow up until results return to normal or to pre-treatment levels. In case of an SAE, a Serious Adverse Event Form should be completed and reported to the Hospital Medical Ethics Committee and the IIT Project Management Office within 24 hours.

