### **\*\*6.2 Efficacy Analysis and Statistical Methods\*\***

Statistical analysis will be performed using R software. For demographic and baseline characteristics, continuous variables conforming to normal distribution will be expressed as mean  $\pm$  standard deviation ( $\bar{x} \pm s$ ) and compared between groups using independent samples t-test; if not normally distributed, they will be expressed as median and interquartile range (IQR) and analyzed using Mann-Whitney U test. Categorical variables will be compared using Chi-square test or Fisher's exact test based on sample size and expected frequencies.

For primary and secondary outcome measures (e.g., FMA-UE, FMA-LE, WMFT, BBS, MBI scores), Linear Mixed Effects Models (LMM) will be used to handle repeated measures data, implemented via the "nlme" package in R, to assess changes over time and differences between groups, accounting for correlations within subjects across multiple time points. Post-hoc subgroup analyses will explore differential efficacy of taVNS across different stroke types (ischemic vs. hemorrhagic) and lesion locations.

For safety indicators, normality tests will first be performed on Heart Rate Variability (HRV) and blood pressure data. If normally distributed, paired sample t-tests will be used to compare values before and during treatment; if not, Wilcoxon signed-rank test will be used. Comparison of adverse event incidence rates between groups will use Chi-square test or Fisher's exact test.  $p < 0.05$  will be considered statistically significant.

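### HRV and blood pressure are tested only within arm, and the adverse-event definition and the safety objective do not fit the three-arm safety comparison

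*Protocol*

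**What the plan says.** **HRV and blood pressure.** Protocol section 6.2 calls these safety indicators. After a normality check, "paired sample t-tests will be used to compare values before and during treatment", with the Wilcoxon signed-rank test otherwise. It states no between-arm test for them, and does not say whether the second reading is taken within a session or over the 4-week course. The data-collection list in section 3.6 mentions neither measure.

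**Aim and arms.** Section 3.3 gives the purpose as the efficacy and safety of bilateral taVNS and how it differs from left-sided taVNS. The conventional arm is described as: "Based on drug therapy, provide conventional rehabilitation treatment for stroke hemiplegic motor dysfunction, including comprehensive rehabilitation such as exercise therapy", among other therapies. No taVNS and no sham is listed for it.

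**Adverse events.** Section 4.1.1 defines an adverse event as an untoward occurrence "in a subject temporally associated with the use of the investigational intervention, regardless of whether it is considered causally related". A serious one is "An adverse event occurring during the study that meets one or more of the following criteria". Section 4.2 has the investigator "requiring the subject to truthfully report any changes in condition after receiving the intervention treatment", and also says: "For any AE occurring during the study, details such as time of onset, symptoms, duration, measures taken, and outcome should be recorded". Section 6.2 then plans the test: "Comparison of adverse event incidence rates between groups will use Chi-square test or Fisher's exact test".

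**Objective.** Section 2.2 reads: "To study the safety of unilateral taVNS in treating stroke patients". The synopsis, part (3) of the background and section 3.3 all state the safety aim for bilateral taVNS.

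**The concern.** The trial randomises to three concurrent arms, but the only test fixed for HRV and blood pressure does not use the randomisation. A before-versus-during change mixes any effect of stimulation with everything else that changes in the same interval: rest, time, drugs, rehabilitation. It also gives one answer per arm and none about the difference between arms. A significant change could be read as an effect of taVNS when it is not one. Significance in one taVNS arm but not the other could be read as a difference between them.

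The adverse-event wording creates a second, smaller difficulty. The definition and the question put to patients both start from an intervention that one of the three compared groups does not receive. If sites follow the wording literally, events in the conventional arm may be recorded less completely than in the taVNS arms, and the planned incidence test would then partly measure recording.

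Third, the formal safety objective omits the experimental arm.

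**Working it through.** The protocol gives no safety rate, safety variance or safety sample size, so there is no figure of its own to reproduce. The checks below compare the passages and add illustrations on stated assumptions.

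**1. What each HRV or blood-pressure test estimates.** In arm k, write the mean change as τ_k + δ. Here τ_k is the effect of stimulation, and δ is the change from all other causes, the same on average in every arm because of randomisation.

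- Paired test in arm k: tests τ_k + δ = 0.
- Bilateral minus left: (τ_B + δ) − (τ_L + δ) = τ_B − τ_L, the difference named in section 3.3.
- Bilateral minus conventional: (τ_B + δ) − (0 + δ) = τ_B, provided the control readings are taken at matched times and conditions.

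Only the between-arm contrasts remove δ.

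**2. Illustrated size.** Inputs: 38 patients per arm, or 34 after dropout (section 6.1); level 0.05 (section 6.2), taken as two-sided. Assumption: no effect of stimulation, and a shift δ of 0.2, 0.3 or 0.5 SD of the paired differences. The paired t-test has n − 1 degrees of freedom and noncentrality d√n; for n = 38 this is 1.23, 1.85 and 3.08.

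| Assumed shift (SD of differences) | Chance of p < 0.05, n = 38 | n = 34 |
|---|---|---|
| 0.2 | 22.5% | 20.5% |
| 0.3 | 43.7% | 39.7% |
| 0.5 | 85.1% | 80.8% |

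Reading the two taVNS arms side by side does not rescue the test. If both have the same 0.3 SD shift, the chance that exactly one reaches significance is 2 × 0.437 × (1 − 0.437) = 0.49, although the arms do not differ.

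**3. Adverse events, passages side by side.** Section 4.1.1 requires a time relation to the investigational intervention. Section 4.2 asks about changes after it. Section 3.3 gives the conventional arm none. Section 6.2 compares incidence between groups. On a literal reading, a control patient has no reference point from which an event can count.

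**4. Conditional size for adverse events.** Suppose the control count were zero by definition. The two-sided Fisher p-value for x/38 versus 0/38 is 2 × C(38,x)/C(76,x).

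- x = 5: 2 × 501,942/18,474,840 = 0.054.
- x = 6: 2 × 2,760,681/218,618,940 = 0.025.

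Six events are therefore enough. With the same true rate in both arms, the chance of a false difference is P(X ≥ 6) for X binomial(38, rate).

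| Assumed true rate in both arms | Control count zero by definition | Counted alike in both arms |
|---|---|---|
| 10% | 17.5% | 1.5% |
| 20% | 80.0% | 2.7% |
| 30% | 98.6% | 3.0% |

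At a true rate of 5% the chance is only 1.1% even with a zero control count.

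**5. Objective.** Section 2.2 names unilateral taVNS; the synopsis, background part (3) and section 3.3 name bilateral. These cannot all stand as the safety objective.

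**The case against.** On HRV and blood pressure, a before-versus-during comparison is a recognisable check of tolerability during stimulation, and section 6.2 does not claim that it attributes a change to taVNS. That stands as a reason to keep showing the paired change. It does not make it sufficient: it is the only test section 6.2 fixes for these indicators, and it cannot answer the bilateral-versus-left question in section 3.3. A separate statistical analysis plan could add a comparison, but section 6 is itself headed as the statistical analysis plan and names the test.

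On adverse events the other side is stronger. Section 4.2 has any event during the study recorded, with no arm excluded. The serious-event definition uses the same period. The between-group test in section 6.2 presupposes counting in every arm. Investigational intervention is never defined by arm, and section 3.3 lists the conventional group under its heading on groups and interventions. The synopsis also speaks of sham and section 3.5 of double-blinding, although section 3.3 lists no sham. All this stands as evidence that the intent was probably to count in all arms. It does not remove the conflict, because sections 4.1.1 and 4.2 use the defined term adverse event in those very sentences and so carry its reference to the intervention with them.

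On section 2.2, the mismatch looks like an isolated slip, since three other places state the bilateral aim. That is fair, and it is why this is the least of the three points.

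**Conclusion.** The main point holds as a matter of method: the fixed HRV and blood-pressure test is within arm and cannot show either an effect attributable to taVNS or a difference between bilateral and left-sided stimulation. The probabilities given for it depend on assumed shifts, because the protocol gives none.

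The adverse-event point holds as an ambiguity that conflicts with the planned between-group test. The size of any bias is unknown. The figures of about 18%, 80% and 99% are the extreme case, conditional on the assumed rates and on a control count of zero by definition. Partial under-counting would push in the same direction by less. The objective in section 2.2 plainly disagrees with the rest of the protocol.

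A reader might go further and infer that the safety comparison has no valid control, or that the safety of the bilateral arm could not be validly estimated in either direction. The documents do not support that. There is a concurrent randomised control and a planned between-group test of adverse events. The bilateral-versus-left comparison of adverse events is unaffected by the definition, since both arms receive taVNS, and incidence within the bilateral arm can be estimated on any reading. Nor do the documents show that control-arm events would go unrecorded. The point merits correction but does not undermine the trial's safety assessment as a whole.

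**What to change.** **Section 6.2.** Compare the during-treatment HRV and blood-pressure values between arms, adjusted for the pre-treatment value (ANCOVA or a linear mixed model). State when the during-treatment reading is taken. Make bilateral versus left-sided the like-for-like contrast. Compare each with the conventional arm only where control readings are taken at matched times and conditions; resting values at a visit are not a fair comparator for values taken during a stimulation session. Show the paired changes by arm descriptively. The bilateral-versus-left contrast needs no new data. The contrasts with the conventional arm cost some HRV and blood-pressure readings in that arm.

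**Sections 4.1.1 and 4.2.** Define an adverse event as any untoward medical occurrence in any randomised participant from randomisation to T3, in all arms, and elicit it with the same non-leading question at the same contacts in all arms. The cost is protocol wording and the same question put to control patients, including at the T3 phone or clinic contact.

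**Section 2.2.** Reconcile the safety objective with the synopsis, background part (3) and section 3.3 so that it covers bilateral and left-sided taVNS. The cost is one sentence.

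The analysis change can be made at any time before analysis. The adverse-event question and the control readings help only for patients still to be followed, so they should be changed first.

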### **\*\*3.2 Study Population\*\***

#### **\*\*3.2.1 Inclusion Criteria\*\***

- (1) Age between 18 and 65 years;
- (2) Diagnosed with stroke (including ischemic stroke and hemorrhagic stroke) by a qualified clinician according to the "Chinese Stroke Prevention and Treatment Guidelines" from 2021 onwards;
- (3) Stroke recovery period, stable vital signs, no disease progression;
- (4) Presence of limb motor dysfunction, diagnosed with hemiplegia.

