#### **\*\*3.2.3 Withdrawal Criteria\*\***

- (1) Patient's condition changes requiring transfer to another department or inability to complete standardized treatment;
- (2) Unstable vital signs during treatment or recurrence of stroke;
- (3) Intolerance to taVNS treatment, etc.

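### Section 4.1.1 lets stroke worsening that the investigator judges expected leave the adverse event record, the serious event report and the between-arm safety comparison, with no criterion and no log

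*Protocol*

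**What the plan says.** Section 4.1.1 of the protocol opens with a broad definition: "Any untoward medical occurrence or worsening of a pre-existing medical condition in a subject temporally associated with the use of the investigational intervention", whether or not a causal link is suspected. The same paragraph ends with an exception: worsening of the disease under study, together with its symptoms or signs, "if judged by the investigator to be expected, is not considered an AE". An SAE is then defined as "An adverse event occurring during the study that meets one or more of the following criteria".

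Section 4.2 requires onset, symptoms, duration, measures, outcome and relatedness to be recorded for any AE, and SAEs to be reported within 24 hours. Section 6.2 states: "Comparison of adverse event incidence rates between groups will use Chi-square test or Fisher's exact test", at the 0.05 level.

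Three other places bear on the point:
- Section 3.2.1 admits patients with "Stroke recovery period, stable vital signs, no disease progression".
- Section 3.2.3 lists "Unstable vital signs during treatment or recurrence of stroke" among the reasons for withdrawal.
- On blinding, section 3.5 says the trial is double-blind and the synopsis calls it sham-controlled. Section 3.3 describes a conventional arm without a device, an arm stimulated at the left ear and an arm stimulated at both ears.

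**The concern.** The exception is a rule about what is collected, not a gap in the analysis description. A worsening that is not an AE cannot be an SAE, and section 4.2 does not require it to be written down. No later analysis document can recover an event that was never recorded.

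The rule suits this trial poorly. Safety is part of the objective in the synopsis and is the secondary objective in section 2.2. Neurological deterioration is one of the main things that a safety evaluation of nerve stimulation after stroke should be able to see. Because patients enter in recovery without progression, an exemption for expected worsening has little legitimate use.

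Two things are at stake. The first is loss of information: a real excess of worsening under stimulation could be thinned out of the record. This needs no bias between arms. The second is differential counting, which arises only if the judgement varies with the arm. The protocol does not say that the person judging AEs is blinded.

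**Working it through.** **Tracing one event through the text.** Take a patient whose hemiparesis worsens in week 3.
1. Under the first sentence of 4.1.1 this is an AE: a pre-existing condition has worsened in temporal association with treatment.
2. Under the last sentence of the same paragraph it stops being an AE if the investigator judges it expected. No criterion is supplied.
3. Under the SAE definition it cannot be serious, because it is not an AE. The 24-hour report in 4.2 is not triggered, even if hospital stay is prolonged.
4. Under 4.2 no entry is required, so no log of removals exists.
5. Under 6.2 it is absent from the incidence comparison.

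Steps 2 to 5 do not depend on who is blinded.

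**Size.** The protocol gives no AE rate, no power for the AE comparison and no share of events likely to be judged expected, so there is no stated figure to reproduce. What follows is an illustration.

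Inputs: n = 38 per arm (section 6.1); two-sided 0.05 (6.2 gives the level but not the sidedness); Fisher's exact test on two arms, by exact enumeration of two binomials. Assumed: risk of other AEs *o*, risk of stroke worsening *w*, the two independent, and share *q* of worsenings removed. Only worsening can be removed, as the clause says. The counted rate is

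p = 1 − (1 − o)(1 − w(1 − q)).

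*Masking of a real excess.* o = 10% in both arms; w = 5% in control and 30% with stimulation.

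| Removal | Control p | Stimulated p | Power |
|---|---|---|---|
| None | 1 − 0.90 × 0.95 = 14.5% | 1 − 0.90 × 0.70 = 37.0% | 53% |
| Half, stimulated arm only | 14.5% | 1 − 0.90 × 0.85 = 23.5% | 11% |
| Half, both arms | 1 − 0.90 × 0.975 = 12.25% | 23.5% | 17% |

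With w = 10% in control instead of 5%, power falls from 33.6% with no removal to 4.5% with half removed in the stimulated arm only.

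*False differences under equal true risk.* Remove 70% of worsenings in one arm and 20% in the other.
- With o of 5%, 10% or 20% and w of 2%, 5% or 10%, the rejection rate is 0.6% to 4.6%. Example, o = w = 10%: counted rates are 1 − 0.90 × 0.92 = 17.2% and 1 − 0.90 × 0.97 = 12.7%, and the rejection rate is 4.6%, against 2.7% with no removal.
- With w = 20% it is 8% to 13%.
- With all worsenings removed in one arm and none in the other, it is 0.9% to 4.3% for w of 5% or less, and 8% to 15% for w = 10%.
- Equal removal leaves the level about where it was: at o = 10% and w = 20%, 2.9% with none removed and 2.7% with half removed in both arms.

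**The case against.** The strongest reply has five parts.

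*The clause is narrow.* It reaches only worsening of the stroke; device effects and general medical events are counted as usual. This stands, and it is why the illustration removes only worsening. A reader might infer that the whole AE comparison is discretionary. The text does not support that.

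*Few events would qualify.* If patients enter without progression, worsening should be uncommon and little of it could properly be called expected. This stands as far as it goes: applied strictly, the clause might remove little. But nothing in the protocol makes the application strict, and a clause with so little proper use is easily given up.

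*The trial is declared double-blind.* A reader might infer from section 3.3 that the investigator knows the arm. That is a reasonable inference, since no device, one ear and two ears look different and no sham is described. It is not a statement in the protocol, and it conflicts with section 3.5 and the synopsis. What can be said is that the passages disagree and that blinding of the AE assessor is not stated.

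*Recurrence is not exempted.* A reader might infer that a recurrent stroke can be dropped as expected worsening. The text does not say so. Recurrence is a withdrawal reason, and a new stroke fits the first sentence of 4.1.1. The protocol does not say explicitly that it is recorded as an AE, so one sentence is worth adding.

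*Worsening shows elsewhere, and a later document can define expected.* The motor, balance and daily-living scales at T0, T1 and T2 would register lasting deterioration. Scores at fixed visits are not events, however: they carry no seriousness or relatedness judgement and trigger no report. A later definition could narrow the discretion, but the protocol text as it stands still removes the event from the record.

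**Conclusion.** The point holds as a defect in what is recorded. Section 4.1.1 contradicts its own opening sentence for the disease under study, gives no criterion for the exception, and passes the loss on to SAE reporting and to the section 6.2 comparison. None of this requires bias between arms.

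The effect cannot be sized from the document. On the assumed rates, removing half of the stimulated arm's worsenings cuts power from 53% to 11%. Removing half in both arms still cuts it to 17%. These figures assume a large true excess (30% against 5%), independence of worsening and other AEs, and 38 evaluable patients per arm.

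A reader might go further and infer that the clause will produce spurious safety differences. The figures do not support that in general: the rate stays under 5% for 70% against 20% removal when worsening is 10% or less. It becomes material only if worsening is common or removal is extreme and one-sided. Differential counting is possible but not shown.

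Weight: a cheap improvement, best made before enrolment because the loss cannot be repaired afterwards.

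**What to change.** 1. Delete the exception for expected worsening from section 4.1.1.
2. State that all neurological worsening is recorded as an AE in all three arms. The conventional arm should be named, because the definition ties AEs to use of the investigational intervention, which that arm does not receive.
3. State that stroke recurrence is recorded as an AE, in addition to being a withdrawal reason under section 3.2.3.
4. Add expectedness as a separate field on the case report form.
5. Run the section 6.2 comparison on all events, with a second tabulation that leaves out those marked expected.

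The cost is a wording change, one form field and one extra table. The downside is somewhat more events to record and report.
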